Our exploratory aim is to examine the relationships between CG primary and secondary outcome changes and their potential mediators (eg, adherence) and moderators (eg, sleep change in persons with dementia, interpersonal processes, and shared lifestyle factors).

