### Randomization and Blinding

Computer randomization will be performed by the team’s biostatistician, using a permuted block randomization technique stratified by baseline sleep medication use (yes or no) [36]. Other personnel (except for therapists, supervisor, and project coordinator) will be blinded to randomization.

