	**Utility and treatment satisfaction**		
		Internet Intervention Utility Questionnaire [38]	This is a 16-item measure designed to assess usability, likeability, usefulness, understandability, and convenience of an internet intervention using a 5-point Likert scale, ranging from 0 (not at all) to 4 (very); 2 additional open-ended questions ask about the most and least helpful aspects of the program.
		Satisfaction Survey	This is a 9-item measure designed to provide feedback on the study, including its structure, assessments, scheduling, working with study staff, and the usability of the intervention platforms using a 10-point Likert scale, ranging from 1 (strongly disagree) to 10 (strongly agree), and open-ended questions.

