	**Nighttime behaviors of persons with dementia**		
		Neuropsychology Inventory Nighttime Behavior Scale [56]	This is an 8-item measure designed to assess frequency and severity of detrimental sleep behaviors, such as wandering, in the dementia patient using yes or no questions.

^a^HRV: heart rate variability.

^b^RMSSD: root mean square of successive RR interval differences. RR interval is the time between 2 detected heartbeats, calculated for every QRS event.

^c^pNN50: The proportion of NN50 divided by the total number of NN (R-R) intervals. NN50 is the number of times successive heartbeat intervals exceed 50 ms. RR interval is the time between 2 detected heartbeats, calculated for every QRS event. NN interval is the time (normalized) between 2 detected heartbeats, calculated for every QRS event.

^d^HR: heart rate.

^e^LF: low frequency.

^f^HF: high frequency.

^g^SF-36: Short Form-36 Health Survey Questionnaire.

^h^CRP: C-reactive protein.

^i^IL-6: interleukin-6.

^j^Aβ: plasma amyloid beta.

^k^p-tau: phosphorylated tau.

**Table 2 table2:** Schedule of outcome measures.

	Baseline	Treatment	After treatment	Boosters	6-month follow-up	12-month follow-up
Assessment period, weeks	1	4	1	1	1	1
Screening, apnea testing, consent and assent, and demographics	✓					
HRV,^a^ ISI,^b^ PSS,^c^ KCGSS,^d^ inflammation and neurodegeneration biomarkers, cortisol, actigraphy, SF-36,^e^ BDI,^f^ STAI,^g^ DBS,^h^ ZBS,^i^ QoL,^j^ daily Joggle battery, NIH Toolbox for Assessment of Neurological and Behavioral Function, CFQ,^k^ P-CG FUS,^l^ G-S L-T PAQ,^m^ fruit and vegetable servings per day, respite, secondary CG^n^ outcomes, DSRS,^o^ NPI,^p^ and NBS^q^	✓		✓		✓	✓
Electronic daily diaries	✓	✓	✓	✓	✓	✓

^a^HRV: heart rate variability.

^b^ISI: Insomnia Severity Index.

^c^PSS: Perceived Stress Scale.

^d^KCGSS: Kingston Caregiver Stress Scale.

^e^SF-36: Short Form-36 Health Survey Questionnaire.

^f^BDI: Beck Depression Inventory.

^g^STAI: State-Trait Anxiety Inventory.

^h^DBS: Dysfunctional Beliefs about Sleep.

^i^ZBS: Zarit Burden Scale.

^j^QoL: Quality of life of caregiver of patient with dementia.

^k^CFQ: Cognitive Failures Questionnaire.

^l^P-CG FUS: Patient-Caregiver Functional Unit Scale.

^m^G-S L-T PAQ: Godin-Shephard Leisure-Time Physical Activity Questionnaire.

^n^CG: caregiver.

^o^DSRS: Dementia Severity Rating Scale.

^p^NPI: Neuropsychological Inventory.

^q^NBS: Nighttime Behavior Scale.

**Table 3 table3:** Schedule of process measures.

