##### Testing of Aim 1: Feasibility and Acceptability of NiteCAPP CARES and NiteCAPP SHARES

The feasibility and acceptability of NiteCAPP CARES and NiteCAPP SHARES will be evaluated using average completion rates (number of sessions completed), adherence (measured through sleep diaries and logs), and satisfaction and utility ratings. These variables will be compared for NiteCAPP CARES and NiteCAPP SHARES using independent samples 2-tailed *t* tests.

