##### Testing of Aims 2 to 4: Primary and Mechanistic and Secondary Outcomes

A mediated GEE model [58] (clusters are individuals measured over 4 time points) will test causal paths between intervention effects on the primary and secondary outcomes (Figure 3). On the basis of a priori hypotheses, separate GEE models, including group (NiteCAPP CARES and NiteCAPP SHARES), time (baseline, after treatment, and 6-month and 12-month follow-ups), and their interaction as predictors, will be conducted for each primary CG outcome (aim 2: insomnia severity, sleep onset latency, wake after sleep onset, sleep efficiency, arousal, and inflammation), secondary CG outcome (aim 3: health, mood, burden, and cognitive performance), and secondary outcome for persons with dementia (aim 4: actigraphy total wake time for persons with dementia). Potential covariates affecting the mechanistic outcomes (Table 2) or technology use by CGs and persons with dementia (eg, Internet Intervention Utility Questionnaire [38]) will be assessed and used as covariates if significant.

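### The covariate rule for Aims 2 to 4 admits measures taken after randomisation and picks them by significance; it should be limited to prespecified baseline values

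*Protocol article*

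**What the plan says.** The section on testing Aims 2 to 4 fits a separate GEE for each outcome, with group, time (baseline, post-treatment, 6 and 12 months) and their interaction. It then opens the model to covariates from two sources. The first is "Potential covariates affecting the mechanistic outcomes (Table 2"), and the second is "technology use by CGs and persons with dementia (eg, Internet Intervention Utility Questionnaire [38]) will be assessed and used as covariates if significant". No time point is set for either source.

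Four other places bear on this rule:

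- Table 1 describes the questionnaire as a "16-item measure designed to assess usability, likeability, usefulness, understandability, and convenience of an internet intervention" and lists it under Aim 1.
- The Aim 1 test plan covers "satisfaction and utility ratings. These variables will be compared for NiteCAPP CARES and NiteCAPP SHARES using independent samples 2-tailed" *t* tests, so utility is itself compared by arm.
- Table 2 has a baseline-only row (screening and demographics), a diary row, and one row holding nearly everything else, including "inflammation and neurodegeneration biomarkers, cortisol, actigraphy". That last row is ticked at baseline, post-treatment, 6 months and 12 months.
- Tests of Hypotheses commits to intention to treat with every randomised participant.

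Allocation is made "using a permuted block randomization technique stratified by baseline sleep medication use (yes or no"). That stratum is not among the named model terms.

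**The concern.** A covariate that the arm can change is not a neutral adjustment variable. If the CBT-I arm finds its program more useful, and people who find it useful also sleep better, holding utility fixed removes part of the effect under test. If there is no effect, it creates an apparent one in the opposite direction. The same applies to any Table 2 measure used at its post-treatment or follow-up value, since many of these are outcomes expected to respond to treatment.

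Entry by significance adds a second problem: the form of the primary model depends on the data and may differ between outcomes. A third is that a participant who never used the program has no utility score, and a model that needs one will by default leave that person out.

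This is more than detail left to an analysis plan. The article states a selection rule and gives an example that should not be in it.

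**Working it through.** **Timing.** The utility questionnaire is in neither schedule table (Tables 2 and 3), so its timing is inferred from its content. A rating of a program's usability and usefulness can be given only after the program has been used, hence after randomisation.

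**Size.** The article gives no figure to reproduce, so this is an illustration. Inputs from the article are an analysed sample of 80, four time points and an autoregressive correlation of 0.5 (Power Analysis). Assumed inputs are:

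- 40 per arm;
- an arm shift *d* in the covariate of 0.3 to 0.8 SD;
- a within-arm correlation *r* with the outcome of 0.3 to 0.5;
- a true effect of 0 or 0.63 SD. With 40 per arm, 0.63 SD gives 80% power in a simple two-group comparison.

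Formulas for the bias in the group x post-treatment term:

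- Covariate measured at every visit and shifted by treatment: bias = −*d* × *r*.
- Single post-treatment score with a score x time term: bias = −*d* × *r* × (1 − 0.5). The score correlates *r* with the post-treatment outcome and 0.5*r* with the baseline outcome, so its slope on the change is 0.5*r*.
- Single score as a main effect only: bias = 0 with complete data, because a person-constant term cancels from within-person change.

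Simulated group x post-treatment estimates (600 runs, robust standard errors), with formula values for the bias in brackets:

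| *d*, *r* | True effect | No covariate | Score, main effect | Score x time | Time-varying covariate |
|---|---|---|---|---|---|
| 0.3, 0.3 | 0 | −0.010 | −0.010 | −0.052 (−0.045) | −0.094 (−0.09) |
| 0.5, 0.3 | 0 | −0.002 | −0.002 | −0.075 (−0.075) | −0.154 (−0.15) |
| 0.5, 0.5 | 0 | 0.005 | 0.005 | −0.120 (−0.125) | −0.244 (−0.25) |
| 0.8, 0.5 | 0 | 0.003 | 0.003 | −0.191 (−0.20) | −0.399 (−0.40) |
| 0.3, 0.3 | 0.63 | 0.639 | 0.639 | 0.595 | 0.547 |
| 0.8, 0.5 | 0.63 | 0.623 | 0.623 | 0.415 | 0.225 |

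With the time-varying covariate, type I error runs from 0.063 to 0.458, against 0.038 to 0.047 with no covariate. At a true 0.63, power falls to between 0.69 and 0.16, against 0.74 to 0.80. With the score x time term, type I error is 0.04 to 0.10 and power 0.71 to 0.37.

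**Single-visit contrast with entry only if significant** (2,000 runs, *d* from 0.3 to 0.8). At a true 0 the mean estimate is −0.07 to −0.40 and type I error is 0.06 to 0.44. At a true 0.63 it is 0.56 to 0.23. The covariate was retained in about three quarters of runs at *r* = 0.3 and in 99% or more at *r* = 0.5, so the significance filter gives little protection. With *d* = 0 there is no bias.

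**Stratum.** Assume a 0.5 SD stratum effect and 40% medication users. Leaving the stratum out of the single-visit model does not change the estimate (0.626 with and without it) and costs about 1 to 2 points of power. In the group x time GEE with complete data, adding it left the estimate (0.620) and robust standard error (0.220) unchanged.

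**The case against.** The strongest reply is that the article never says post-baseline values will be used. Table 2 includes a baseline-only row, and its repeated row holds measures such as dementia severity and respite that have usable baseline values. In the model as described, one utility score entered as a main effect does no harm to group x time. All inputs for size are assumed, and how missing covariates are handled is not stated and may be settled in the analysis plan.

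Much of this stands, and it limits the point to what the rule permits. It does not rescue the rule. The one covariate named has no baseline value, and nothing excludes the harmful forms.

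A reader might also infer three stronger things that the documents do not support:

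- *That leaving out the stratification factor biases the effects.* It does not. At most it costs a little precision in a single-visit model, and naming it is commonly left to the analysis plan.
- *That the moderators bias Aims 2 to 4.* The exploratory aim names "moderators (eg, sleep change in persons with dementia, interpersonal processes, and shared lifestyle factors"), and the Figure 1 legend places sleep change in the person with dementia as a moderator of the relation between caregiver outcome changes. A moderator measured after randomisation makes that exploratory relation hard to interpret, but it does not enter the Aims 2 to 4 effect models.
- *That a shrinkage calculated for a single-visit regression carries over to any utility adjustment.* It does not carry over to a lone main effect in the group x time model.

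**Conclusion.** The covariate rule is wrongly drawn. It names a post-randomisation rating that is also an Aim 1 outcome, draws other covariates from measures mostly repeated after randomisation, sets no limit to baseline, and selects by significance. Bias in the Aims 2 to 4 effects is possible, not certain. It requires that the arm shifts the covariate and that the covariate enters as time-varying, with a time interaction or in a single-visit contrast.

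Under the assumed shifts and correlations, the bias is about 0.1 to 0.4 SD for time-varying covariates and single-visit contrasts, and about 0.05 to 0.2 SD for a utility x time term. Its direction depends on the signs assumed; here a covariate that improves with treatment and goes with better outcomes pulls the estimate down. Even in the harmless form, loss of participants without a utility score would sit badly with the commitment to analyse everyone randomised. That loss is the usual software default and is not something the article states.

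**What to change.** In the section on testing Aims 2 to 4:

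- Delete the rule that covariates enter on significance, and delete the utility questionnaire as an example.
- Name one covariate set in advance, limited to values measured before randomisation. Include the baseline sleep-medication stratum, for consistency with the randomisation and not to remove bias.
- State that utility, adherence and other post-randomisation measures are used only for Aim 1 and in the mediation models. The planned mediated GEE needs such variables and is unaffected.
- Do not add the baseline outcome as a covariate while baseline is one of the modelled time points, since the same value would then stand on both sides of the model.

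The cost is a wording change before unblinding, with no new data. The one small loss is the freedom to choose covariates after seeing the data.

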**Figure 3 figure3:**
[figure not shown]
Mediated generalized estimating equations model. Analyses will also be conducted examining the paths from after treatment to 6-month follow-up and from 6-month follow-up to 12-month follow-up. Base: baseline; CG: caregiver; F6: 6-month follow-up; F12: 12-month follow-up; NiteCAPP CARES: cognitive behavioral therapy for insomnia; NiteCAPP SHARES: active web-based sleep hygiene and related education control; Post: after treatment.

##### Testing of Exploratory Aim

We will evaluate primary and secondary outcome change relationships and their potential mediators and moderators (Table 2). Mediated GEE will be used to compare NiteCAPP CARES versus NiteCAPP SHARES. Moderating effects will be tested using interactions (Table 2).

### Missing Values

The SAS PROC GEE weighted model handles missing data completely at random or at random. When measures are collected over time, some participants may not complete the study. Unlike repeated measures ANOVA, which excludes them from analysis, weighted GEE retains them (increasing power and producing unbiased estimates).

### Patient and Public Involvement

Patients and the public are not involved in any of the following study procedures: development of research questions and outcome measures or plan for results dissemination. The Community Advisory Board (CAB) will assess the burden of the intervention and may help with recruitment. Every participant will fill out a patient satisfaction and experience survey after treatment and at 6-month and 12-month follow-ups. This questionnaire asks CGs and persons with dementia which modules were most and least useful for them, how they felt about the length of the program, suitability for CGs and persons with dementia, and so on. Trial results will be communicated to participants and the public through peer-reviewed manuscripts.

### Ethics Approval

All procedures were approved by the University of Missouri Institutional Review Board on May 6, 2021 (2053682); safety officer [name] on November 24, 2021; the National Institute of Aging (NIA) on January 26, 2022; and the University of South Florida Institutional Review Board on March 10, 2022 (003936). The NIA and the safety officer reviewed and approved the study protocol, manual of operating procedures, informed consent form, and monitoring plan with emphasis on data integrity and patient safety issues in November 2021. The safety officer will review these biannually. Any changes to these procedures that are recommended by the safety officer will be adopted with institutional review board and NIA approval. The safety officer will review adverse events and monitor study results, focusing on efficacy, recruitment progress, randomization, compliance, retention, protocol adherence, operating procedures, forms completion, intervention effects, participant safety, and minority inclusion. The principal investigator ([name]) registered the study with ClinicalTrials.gov (NCT04896775) on May 21, 2021, and will submit annual reports to the funding agency.

Our team includes a CAB comprising 8 CGs, 4 persons with dementia, and 4 local experts. The CAB structure and procedures are based on the CAB Toolkit described by Kubicek and Robles [59]. The CAB will meet twice each year, with each meeting lasting 2 hours (respite care costs for persons with dementia will be paid by the grant). The team includes a consultant CG advocate who is a trained facilitator, and she will facilitate the CAB meetings.

## Results

This work is supported by the National Institutes of Health’s NIA (R01AG066081). Recruitment procedures started in February 2022. All data are expected to be collected by 2026. Full trial results are planned to be published by 2027. Secondary analyses of baseline data will be subsequently published.

We will present the findings at national conferences, including the Associated Professional Sleep Societies (APSS or SLEEP) and the Gerontological Society of America, in the final year of the project. An abstract reporting the findings of the preproposal focus group was presented at the August 2020 internet-based SLEEP meeting, and a brief report based on these findings is currently under review. The web-based treatment materials will be shared electronically and will be widely available to clinicians. The findings will also be disseminated to the dementia and dementia caregiving communities through websites and other resources. The team’s community CG advocate and CAB will be involved in planning for broad dissemination to the dementia and CG communities. They will also help to ensure that materials used to disseminate findings are written for, and easily understood by, lay audiences in rural areas.

## Discussion

The overarching goal of this RCT is to evaluate the acceptability, feasibility, and short-term and long-term effects of NiteCAPP CARES on the sleep and stress mechanisms underlying poor CG health and functioning. To the best of our knowledge, there is no current web-based CBT-I treatment that is tailored for CGs of persons with dementia and none that involve the person with dementia in treatment.

### Strengths and Limitations

This study includes several strengths. It is a novel 4-week web-based CBT-I (NiteCAPP CARES) in CGs and persons with dementia (using a dyadic approach) that integrates sleep education, sleep hygiene, stimulus control, sleep compression, relaxation, problem solving, coping and stress management, and cognitive restructuring techniques. This study uses a rigorous methodology and NiteCAPP CARES will be examined in comparison with an active web control (NiteCAPP SHARES). Long-term follow-ups at 6 and 12 months will enable examination of the persistence of the behavioral outcomes of NiteCAPP CARES. The potential limitations include participant attrition at follow-up, which may contribute to selection bias associated with systematic differences between participants completing NiteCAPP CARES and those completing NiteCAPP SHARES.

### Future Directions

Future directions for this RCT include a multisite effectiveness trial to determine generalizability across different areas. In addition, once NiteCAPP CARES is enhanced based on the results of this RCT, it needs to be tested within other populations (nonrural CGs and other underserved populations) for broader dissemination. Finally, dismantling studies could examine the most effective components of NiteCAPP CARES treatment to further streamline the treatment.

### Conclusions

This RCT tests NiteCAPP CARES, a web-based CBT-I for rural CGs. The Cognitive Activation Theory of Stress and our research as well as research conducted by others [7,31] support our novel hypothesis that NiteCAPP CARES will improve CG health, mood, burden, and cognition by targeting sleep, arousal, and inflammation. This trial addresses what improves as well as how, why, and for how long (up to 1 year). This trial is a necessary first step, and the results from this study will help us to modify NiteCAPP CARES to optimize treatment potency and support future pragmatic testing and dissemination.

## Appendix

Multimedia Appendix 1 Peer-reviewer report from the Center for Scientific Review Special Emphasis Panel Member Conflict: Stress, Sleep, Disparities, and Aging (National Institutes of Health, USA).

## Abbreviations

ANS: autonomic nervous system
Aβ: plasma amyloid beta
bCBT-I: brief cognitive behavioral therapy for insomnia
CAB: Community Advisory Board
CBT-I: cognitive behavioral therapy for insomnia
CG: caregiver
GEE: generalized estimating equations
HR: heart rate
HRV: heart rate variability
NiteCAPP CARES: cognitive behavioral therapy for insomnia
NiteCAPP SHARES: active web-based sleep hygiene and related education control
RCT: randomized controlled trial
